## Abstract

**Background::**

Tong Jing Tiao Xing tuina (TJTX) is a Chinese massage method. Excising with scalp acupuncture (ESA) is a treatment combining scalp electroacupuncture with physical therapy (PT), and yinao fujian formula (YNFJ) is a Chinese oral herbal granule medicine. The combination of the 3 methods is called the “Zhishen Tiaoxing” (ZSTX) rehabilitation program, which is used as an alternative of limb spasm after stroke. There is little available evidence demonstrating its safety and efficacy.

**Methods::**

This will be a subject-blind, randomized controlled trial conducted in 3 medical centers. It will strictly follow the Standards for Reporting Interventions in Clinical Trials of Acupuncture, 2010. We will recruit 316 patients with limb spasm after stroke, 200 from the Affiliated Hospital of Changchun University of Chinese Medicine, Changchun, China, 80 from the Second Affiliated Hospital of Heilongjiang University of Chinese medicine, Harbin, China, and 36 from Huashan Hospital of Fudan University, Shanghai, China. A block randomization sequence stratified by centers will be generated using SAS Version 9.2 software (SAS Institute, Cary, NC, USA), which was performed at the Guangdong Provincial Hospital of Chinese Medicine's Key Unit of Methodology in Clinical Research. The treatment group is treated with TJTX (once a day), ESA (once a day), and oral YNFJ (twice a day). The control group will be treated with PT. Two groups of patients will be treated 5 sessions a week for 4 weeks, and there will be 6-month follow-up. The outcome evaluators will be blinded to patient grouping. The primary outcome will be modified Ashworth scales. The secondary outcome indexes will be the simplified Fugl–Meyer assessment scale, surface electromyogram root mean square value, modified Barthel index, stroke-specific quality of life scale, health scale of traditional Chinese medicine, visual analogue scale (VAS), and the Hamilton depression scale.

**Discussion::**

The Randomized Controlled Trial (RCT) mainly aim to evaluate the effectiveness and safety of traditional Chinese medicine rehabilitation program, by comparing the treatment of ZSTX with the PT for the treatment of limb spasm after stroke.

**Trial registration::**

Chinese Clinical Trial Registry: ChiCTR 1900024255. Registered on July 3, 2019.

## Introduction

1

Stroke poses a serious threat to human health and life with high incidence and disability rates.^[1–4]^ It is the third most common cause of disability in the world^[5]^ and the number one killer in China.^[6]^ Spasticity, the incidence of which ranges from 17% to 43% in post-stroke patients^[7–9]^ is a common dysfunction, causing pain, affecting the free movement of limbs, and causing joint contractures.^[10–13]^ Spasticity after stroke is a major problem for rehabilitation. It is also a hot topic in international medical research. In 2016 AHA/ASA adult stroke rehabilitation treatment guidelines,^[14]^ oral drugs, normal limb position placement, and botulinum toxin injections were recommended. Nevertheless, there are some limitations in those treatments. Oral antispasmodic drugs act on the whole body but cannot selectively target the spasm site. The effect of botulinum toxin injection lasts no longer than 3 to 4 months, and it is necessary to determine whether continuous botulinum toxin injection is necessary.^[15]^ Although there is consensus among experts regarding intrathecal injection of baclofen, the sample size of the study was small and the technical requirements were high; therefore, it is not widely used.

Acupuncture, Chinese herbal medicine, and tuina have been used for a long time to treat post-stroke limb spasm in China. At present, a large number of hospitals in China use acupuncture, tuina, and other methods in addition to modern technologies for the rehabilitation of post-stroke limb spasm. Systematic reviews^[16–18]^ showed that Traditional Chinese Medicine (TCM) treatments were superior to other therapies; nevertheless, only a few provide sufficient clinical evidence, including high quality randomized controlled trial designs or large sample sizes. There are few high-quality and standardized studies of combinations of comprehensive TCM therapy rehabilitation methods.

Therefore, the purpose of this randomized controlled and assessor-blinded trial protocol is to determine the safety and efficacy of excising with scalp acupuncture (ESA) combined with Tongjing Tiaoxing tuina (TJTX) and Yinao Fujian formula (YNFJ) in rehabilitation of limb spasm after stroke.

## Method and design

2

### Study design

2.1

This study is a randomized, assessor-blinded, Sham-controlled, and parallel clinical trial. From August 2019 to December 2020, we will recruit 316 outpatients or inpatients suffering from limb spasm after stroke, who will be randomly divided into the treatment group (n = 158) and the control group (n = 158) using the central randomized system of clinical research of Guangdong Provincial Hospital of Chinese Medicine in Guangdong. Participants in the treatment group will receive ESA, TJTX, and YNFJ with fixed drug composition and fixed dose, while participants in the controlled group will receive PT.

During the study, we will the participants not to take other drugs that could affect the treatment of spasticity or other treatment methods that might affect the recovery of spasticity during the baseline, treatment, and follow-up periods. The basic drugs for stroke patients (i.e., antihypertensive drugs, hypoglycemic drugs, lipid-lowering drugs, and anti-platelet aggregation drugs) will be permitted. We will evaluate participants during the baseline period and at the second and fourth weeks after randomization (Fig. 1). This protocol will be reported according to recommendations for intervention trials SPIRIT 2013^[19]^ Statement: Defining Standard Protocol Items for Clinical Trials. The test process is designed according to the STICTA 2010^[20]^ report.

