### Blinding method

2.9

Blinding methods will be applied to data statisticians and outcome evaluators throughout the trial. They will not able to obtain information regarding grouping and treatment of participants. Acupuncture and tuina belong to the external treatment of TCM, it is difficult to implement blind method for operators, so clinical therapists do not participate in data collection, statistics, and final outcome evaluation. For the treatment of patients, we will assign different patients to different treatment rooms where the beds are independent so as to avoid contact among patients. We separate personnel who separately in charge of random grouping, clinical treatment, data processing, and outcome evaluation completely, so as to ensure the authenticity of the outcome of the trial to the greatest extent possible.

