**Figure 2 F2:**
[figure not shown]
Acupoints of scalp acupuncture.

The patient lies supine, while the acupuncturist sterilizes Qianding (DU21) with alcohol swabs, inserts the needle into Qianding (DU21) at a 30° angle with the skin, then inserts the needle into the acupoint slowly and smoothly until it is under the cap aponeurosis, penetrating the depth of 25 to 40 mm with the direction to Baihui (DU20). The connection between Qianding (DU21) and Baihui (DU20) is named Line 1. From the left and right 1 cun and 2 cun points of Qianding (DU21), there will be needling along the direction parallel to line 1. From the Positioning XinHui (DU22) point, the acupuncturist inserts the needle into XinHui (DU22) with the same technique as above, penetrating towards Qianding (DU21). The connection between XinHui (DU22) and Qianding (DU21) is named Line 2. From the left and right 1 cun points of XinHui (DU22), the needle direction parallels line 2. Eight needles are used per session.

After the needles have penetrated, we will use electronic acupuncture treatment instrument to connect the acupoints on both sides of Qianding (DU21) and both sides of Baihui (DU20) point, with an intermittent wave of 80 Hz frequency and an intensity of 1 to 10 mA; 30 minutes later, we remove the electric acupuncture. We then maintain the needles in the head for 6 hours during which time the patients receive physical therapy, 5 sessions a week over 4 weeks.

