#### Control group

2.10.2

PT for the control group is the same as that of the treatment group.

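### The trial is labelled subject-blind and sham-controlled, but the control arm is physical therapy alone with no sham described, so participants cannot be blind to their arm

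*Protocol article*

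**What the plan says.** Two places in the protocol article claim a form of control over participants' expectations. The abstract (Methods) says: "This will be a subject-blind, randomized controlled trial conducted in 3 medical centers". Section 2.1 (Study design) says: "This study is a randomized, assessor-blinded, Sham-controlled, and parallel clinical trial".

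The operative sections describe something else. Section 2.1 goes on to say that "participants in the controlled group will receive PT", and section 2.10.2 (Control group) says only: "PT for the control group is the same as that of the treatment group". On who is blinded, section 2.9 says: "Blinding methods will be applied to data statisticians and outcome evaluators throughout the trial". That section also accepts that those delivering acupuncture and tuina cannot readily be blinded.

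The treatment arm receives scalp electroacupuncture, tuina, oral granules and PT. On the needling, section 2.10.1.1 says: "We then maintain the needles in the head for 6 hours during which time the patients receive physical therapy".

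**The concern.** Sham control and participant blinding are specific design properties. They tell a reader that both arms had the same apparent treatment and that expectation was balanced between them. If the trial has neither, the labels overstate what a difference between arms can show.

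Two things are at stake. First, the added components bring extra attention and visible treatment as well as any specific effect, and without a sham these cannot be told apart. Second, outcomes that depend on the participant's own report can shift because the participant knows the arm. The limitations paragraph in the Discussion (section 3) mentions only the difficulty of blinding treating staff. Participants are left out of the stated limits, and the abstract's claim about them goes uncorrected.

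**Working it through.** No arithmetic decides this point. The check sets the labels against the described conduct of the trial.

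1. **Labels.** The abstract says participants are blind. Section 2.1 says there is a sham and that assessors are blinded. The Introduction describes the trial as assessor-blinded only. The document therefore disagrees with itself on who is blind before the interventions are considered.

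2. **What each arm receives.**

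| Component | Treatment arm | Control arm |
|---|---|---|
| Scalp needling | Eight needles, 30 minutes of electrical stimulation, needles kept in for 6 hours (2.10.1.1) | None described |
| Tuina | 30 minutes per session (2.10.1) | None described |
| Herbal granules | Twice a day for 4 weeks (2.10.1.3) | None described |
| PT | Yes (2.10.1.1, 2.10.1.4) | The same PT (2.10.2) |

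The control arm is defined positively, as PT identical to that in the other arm. This is more than a detail lost when the protocol was condensed into an article: the text as written leaves no place for a sham.

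3. **Who is blinded.** Section 2.9 names statisticians and evaluators. The only measure in that section that concerns participants is treatment in separate rooms. That limits contact between patients, but it does not hide from a patient whether needles are in the scalp.

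4. **Can participants be blind?** Section 2.3 says that treatment methods are explained to patients during recruitment. A participant who knows what the trial involves, and then receives either all three added components or none, can tell the arm from the treatment itself. This is an inference, but a firm one.

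5. **Which outcomes are exposed.**
   - The primary outcome, MAS, is graded by the evaluator from resistance during passive movement (2.11.1.1), and evaluators are blinded (2.9).
   - Of the seven secondary outcomes (2.11.2.1 to 2.11.2.7), VAS pain is documented as the patient's own mark.
   - SS-QOL and SF-HSTC concern the patient's own life and health status and are probably patient-reported, although the text does not say who scores them.
   - For HAMD the text does not say who rates it.

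   The count is therefore one documented and two probable, out of seven.

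6. **Extra treatment in one arm.** Over 20 sessions, tuina adds 20 × 30 min = 10 hours and electrical stimulation adds another 20 × 30 min = 10 hours. The added treatment time is 20 hours, with no counterpart in the control arm.

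**The case against.** The best defence is that the methods correct the labels. Sections 2.1 and 2.10.2 name PT as the control, section 2.9 lists exactly who is blinded, and the primary outcome is rated by blinded evaluators. A careful reader would see a PT-controlled, assessor-blinded trial, and nothing in randomisation, outcomes, sample size or analysis depends on the two words. This stands as far as it goes: the operative design is coherent and the primary outcome keeps its main protection. It does not rescue the labels, which sit in the abstract and the design statement and claim properties the trial lacks.

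Three stronger readings are tempting, and the document does not support them.

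- A reader might infer that the abstract misstates the contrast when it describes the aim as "by comparing the treatment of ZSTX with the PT for the treatment of limb spasm after stroke". It does not. The abstract's Background defines ESA as scalp electroacupuncture combined with PT, and ESA is part of ZSTX. PT is therefore in both arms by definition, and the phrase is accurate.
- A reader might infer that most of the secondary outcomes are self-reported. Only VAS is documented as such, and HAMD in particular is not described as self-report.
- A reader might take the 20 hours as extra therapist contact. It is added treatment time. Only the 10 hours of tuina are clearly hands-on, since no therapist attendance is stated for the stimulation period.

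**Conclusion.** The concern holds for the two labels. As described, the trial is neither sham-controlled nor blind to participants. It is open to participants and therapists, with blinded evaluators and statisticians, and it compares ZSTX (which includes PT) with PT alone.

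The consequence is limited but real. Any difference found will be the effect of the whole programme, including attention and expectation. Patient-reported secondary outcomes (VAS, and probably SS-QOL and SF-HSTC) are open to bias from knowledge of the arm. The document gives no ground for saying that the blinded MAS rating is directly biased.

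The conclusion assumes that no sham exists beyond what the article describes. If one does exist, sections 2.1 and 2.10.2 misdescribe the control arm, and the text still has to change.

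**What to change.** - Delete the subject-blind label from the abstract and the sham-controlled label from section 2.1. If a sham is in fact used, describe it and reconcile sections 2.1 and 2.10.2 with it.
- State in the abstract, section 2.1 and section 2.9 that participants and therapists are not blinded, and that outcome evaluators and statisticians are.
- Describe the comparison as ZSTX, which includes PT, against PT alone.
- Add to the limitations in section 3 that the trial cannot separate specific effects of the added components from attention and expectation. Say that patient-reported secondary outcomes are to be interpreted with that limit, and state for SS-QOL, SF-HSTC and HAMD who does the scoring.

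The cost is a change of wording and a less favourable description of the design. Arms, randomisation, outcomes, sample size and analysis are unaffected. The registry record is not available here, so whether it carries the same labels would need to be checked.

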**Figure 1 F1:**
[figure not shown]
Trial flow chart.

### Participants

2.2

We will recruit 316 participants from the departments of Rehabilitation Medicine at 3 hospitals: Affiliated Hospital of Changchun University of Chinese Medicine (Changchun, China), The Second Affiliated Hospital of Heilongjiang University of Chinese Medicine (Harbin, China), and the Affiliated Huashan Hospital of Fudan University (Shanghai, China). Before treatment, we will draw complete blood counts, liver function tests, renal function test, and will obtain urinalyses, electrocardiograms, and other routine tests for the participants to select the patients to be included. In view of the limited mobility of patients with spasticity after stroke, we will recruit patients who are hospitalized at the 3 hospitals. For outpatients who want to participate in the study who meet the selection criteria, we will fully communicate with patients and their family members about everything regarding the trial face-to-face to ensure that they can participate in the entire study, including 6-month follow-up.

### Recruitment

2.3

To recruit participants, we will publicize by such means of recruitment posters, rolling electronic screens, leaflets, radio programs, and WeChat public platforms. During recruitment, we will fully communicate with the patients, clearly informing them of the purpose, significance, test process, treatment methods, and possible benefits and risks of the study. We will then inform the patients and their guardians one-by-one of the contents of the informed consent form. When patients and their guardians completely agree with all the items in the consent form, they will sign it of their own free will.

### Ethical issues

2.4

This study follows the Declaration of Helsinki. The trial has been approved by the relevant institutional review boards (IRBs). On June 13, 2019, the IRB of Affiliated Hospital of Changchun University of Chinese Medicine approved this study (cczyfyl2019 sz-022-1). On December 2, 2019, it passed the ethical review (irb-ap/sc-08/02.0) of the IRB of the Second Affiliated Hospital of Heilongjiang University of Chinese Medicine. Before the trial, we contacted the Chinese Clinical Trial Registry for registration and learned that participants can take part in the project only after they sign informed consent.

### Inclusion criteria

2.5

Patients need to meet the following criteria: the diagnostic criteria of stroke^[21]^; symptoms of increased limb muscle tension, with the modified Ashworth Scale (MAS) score grade 1–2; the course of disease is within 2 weeks to 6 months; age 35–70 years, male or female; conscious and have stable vital signs; and participants or family guardians provide written informed consent.

### Exclusion criteria

2.6

Participants will be excluded if they meet any of the following conditions: other diseases that may cause limb spasm; severe primary diseases of liver, kidney, hematopoietic system, endocrine system, or other complicating diseases that cannot be controlled well; audio-visual abnormalities, severe cognitive impairment, or mental diseases such that the patient cannot cooperate with examination and treatment; pregnancy or lactation; presence of a pacemaker; allergy to metal or severe needle syncope; blood diseases or coagulation disorders; and participation in other clinical studies at the same time.

### Exit criteria

2.7

Participants can withdraw from the trial under any of the following circumstances: participants can withdraw at any time without any reason; death or other major adverse events or accidents occur due to disease development; participants cannot cooperate with the treatment during the treatment process, or change the treatment method in the study, or cannot provide data related to the study; participants who could not complete the 6 months follow-up for any reason.

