### Data analysis contents and methods

2.15

Statistical analysis will be conducted by GPHCM's Key Unit of Methodology in Clinical Research. We will use bilateral test with a significance level of *α* = 0.05, performed using SPSS (SPSS, SPSS Inc., Chicago, IL) version 21.0.

For efficacy evaluation indexes, the data sets of per-protocol analysis (PP) and intention to treat analysis (ITT) will be used. A safety analysis set (SS) will be used for safety evaluation and analysis. Depending on the data type, appropriate statistical methods will be used. First, descriptive statistics will carried out for baseline characteristics of patients. The efficacy evaluation index data are repeated measurement data that can be used for the analysis of variance of repeated measurement. Due to the data missing values caused by withdrawal, the method of multiple filling will be used in ITT analysis. If necessary, the method of missing value processing provided by SPSS version 21.0 can be used to replace data, and various methods will be selected according to the actual situation. For safety evaluation analysis, we will test and compare the incidence of adverse reactions between 2 groups. The severity of adverse reactions and the degree of causality with treatment will be considered in comparison. If the number of adverse reactions is large, the relationship with treatment duration and baseline characteristics will be analyzed.

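### Section 2.7 treats changing treatment or missing the 6-month visit as leaving the trial, which invites avoidable missing data, and section 2.15 does not rank ITT above PP

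*Protocol article*

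**What the plan says.** Section 2.7 (Exit criteria) opens with "Participants can withdraw from the trial under any of the following circumstances" and then gives a list. Besides free withdrawal and death or major adverse events, the list includes "participants cannot cooperate with the treatment during the treatment process, or change the treatment method in the study", inability to provide data, and "participants who could not complete the 6 months follow-up for any reason".

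Section 2.15 (Data analysis contents and methods) says that for efficacy "the data sets of per-protocol analysis (PP) and intention to treat analysis (ITT) will be used". It does not say which set is primary, what PP contains, or what follows if the two disagree. On missing values it says: "Due to the data missing values caused by withdrawal, the method of multiple filling will be used in ITT analysis". It adds that, for replacing missing data, "various methods will be selected according to the actual situation". The efficacy indexes are described as "repeated measurement data that can be used for the analysis of variance of repeated measurement".

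Section 2.11.1.1 schedules the primary outcome, the modified Ashworth scale (MAS), at baseline, weeks 2 and 4, and months 3 and 6 after treatment. Section 2.13 expects 20% dropout.

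**The concern.** Three different events share one label: a participant stops or changes the study treatment, a participant misses a visit, and a participant leaves the study. Only the last has to end data collection. Under section 2.7, someone with all 20 sessions and MAS values at weeks 2 and 4 and month 3 who misses only month 6 falls under an exit criterion. So does someone who changes treatment in week 3, and nothing says that this person is still assessed afterwards.

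Such exits are unlikely to be random. Section 2.1 asks participants to avoid other spasticity treatment through follow-up, and those who respond poorly have most reason to seek it. Exit may also differ by arm. The Abstract calls the trial subject-blind and section 2.1 calls it sham-controlled. Yet section 2.9 blinds only statisticians and outcome evaluators, and section 2.10 compares scalp needles, massage, herbs and physical therapy with physical therapy alone. Participants can probably tell which arm they are in.

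At stake are the month 3 and month 6 comparisons, which would rest on imputation where observation was possible, and the clarity of the efficacy claim if PP and ITT differ.

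**Working it through.** **Inputs** (section 2.13, except the group size of 158, which is also in section 2.1): effective rate 45.5% in control and 65% in treatment; two-sided alpha 0.05 (two-sided from section 2.15); power 90%; 132 per group before dropout; 20% dropout; 158 per group enrolled.

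**1. The plan's own figure.** Unpooled normal formula for two proportions:
n = (z₀.₉₇₅ + z₀.₉₀)² × [p₁(1−p₁) + p₂(1−p₂)] / (p₂−p₁)²
= (1.960 + 1.282)² × (0.455×0.545 + 0.65×0.35) / 0.195² = 131.4, so 132. This matches the plan, so the rates are read as the plan meant them. The planned difference is 65 − 45.5 = 19.5 points.

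**2. How many participants are affected.** 158 × 0.20 = 31.6, about 32 per arm, leaving 158 × 0.80 = 126.4, about 126. Over both arms, 316 × 0.20 = 63.2, about 63. This is an upper figure for what a PP set built on the exit list would omit because of dropout.

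**3. Bounds on the completers' difference.** Assumption, not in the document: every participant in a 20% loss is a non-responder, and loss in an arm not affected this way is random. The completers' rate in an affected arm is p/0.80.
- Treatment: 0.65/0.80 = 81.25%. Control: 0.455/0.80 = 56.875%.

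| Selective loss in | Completers' rates (treatment; control) | Difference | Shift from 19.5 |
|---|---|---|---|
| both arms | 81.25%; 56.875% | 24.4 points | +4.9 |
| treatment arm only | 81.25%; 45.5% | 35.8 points | +16.3 |
| control arm only | 65%; 56.875% | 8.1 points | −11.4 |

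**4. Milder selection, with no true effect.** Assumptions, not in the document: 45.5% response in both arms, 20% lost per arm, control losses random, and a share f of treatment-arm losses being non-responders (random loss is f = 54.5%). The completers' rate in the treatment arm is (0.455 − 0.20(1−f))/0.80. With about 126 completers per arm and the pooled two-proportion test, the chance of a significant result favouring treatment is:

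| f | Completers' rate | Chance |
|---|---|---|
| 54.5% | 45.5% | 2.5% |
| 65% | 48.1% | about 6% |
| 75% | 50.6% | about 13% |
| 85% | 53.1% | about 23% |
| 100% | 56.9% | about 44% |

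If the selection were in the control arm instead, the same figures would apply to a false result favouring control.

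Steps 3 and 4 use an effective rate because that is what section 2.13 plans on. Section 2.15 analyses efficacy by repeated-measures ANOVA, so these figures show scale and direction only and are not a forecast of that analysis.

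**The case against.** The strongest reply is that much of this is silence in a condensed article. The ranking of analysis sets and the definition of PP may stand in an SAP that was not available. Section 2.15 already plans multiple imputation for withdrawals in the ITT analysis, so those participants stay in it. The Discussion plans home visits, a travel subsidy and a reward for completing evaluations, and does not restrict them to participants still on treatment. The opening of section 2.7 is permissive, and the 6-month item can be read as a label for loss to follow-up. Statisticians are kept unaware of grouping (section 2.9), which limits choosing a set by its result.

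Most of this stands. A reader might infer three stronger things, and the document supports none of them as fact:
- *PP consists of 6-month completers, and that result can become the trial's answer.* PP is not defined and no text ties it to the exit list. The inference has some support: imputation is mentioned for ITT only, and a classical repeated-measures ANOVA drops anyone with a missing visit. It is still an inference.
- *Data already collected are discarded, or assessment stops at exit.* Neither is stated.
- *Selective loss would inflate the effect by 16 points.* That needs every treatment-arm loss to be a non-responder and control losses to be random. The same selection in both arms adds about 5 points, and selection in control alone takes about 11 away.

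What the reply does not remove is the exit rule itself. Exit criteria are protocol content, and failing to complete follow-up for whatever reason is a classification rather than a participant's choice. An SAP cannot recover an assessment that was never made, and imputation is weaker than observation when exit depends on outcome.

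**Conclusion.** The point holds in a limited form. Section 2.7 as written merges treatment discontinuation and missed visits with withdrawal from the study. Followed literally, it risks avoidable and plausibly outcome-related missing values at months 3 and 6. Section 2.15 names PP and ITT for efficacy without ranking them and leaves the choice of missing-data method partly open.

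Up to about 32 participants per arm could be affected at the planned dropout. The possible bias in a completers' comparison ranges from about 11 points against treatment to about 16 points in its favour in the one-arm extremes of step 3. Neither its size nor its direction is established. This rests on two assumptions: that exited participants are not assessed further, and that exit is related to outcome. The statement about PP rests on the further inference that PP follows the exit list. The planned imputation protects the ITT result in part. The point therefore calls for a worthwhile, low-cost correction and does not show that the trial's result would be invalid.

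**What to change.** 1. Reword section 2.7 so that stopping or changing the study treatment, or missing a visit, is recorded as such and is not withdrawal from the study. Reserve withdrawal for withdrawn consent, and record the reason and date of each event separately. This concerns data collection only and leaves clinical decisions about treatment untouched.
2. State that all data already collected are kept, and that scheduled assessments continue unless consent is withdrawn, using the home visits and travel subsidy already planned in the Discussion.
3. In section 2.15, name ITT (all randomised participants, as allocated) as the primary efficacy set and PP as supportive. If a separate SAP already does so, refer to it.
4. Do not make attendance at month 6 a condition for PP.

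The cost is protocol and SAP wording, plus a modest number of additional follow-up visits for participants who stop treatment. No sample size changes.
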